#### Statistical analyses

Primary data analysis will be performed in a blinded manner, by conducting the effect analyses without knowing which intervention each of the two groups received. The treatment groups will be examined for baseline comparability. Both parametric and nonparametric statistical analyses will be used, dependent on how the variance is distributed. Effect of the interventions will be analyzed according to intention-to treat principles. Further, exploratory analyses will be performed to study the treatment effect within the three subgroups hip, knee and hand OA.

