Standard treatment for OA in specialist care is an individual consultation with a rheumatologist, sometimes followed by referral to one or several other health professionals. However, many patients with OA experience this provision of health services as fragmented. Due to an increasing demand for a more coordinated approach, a pilot multidisciplinary OA outpatient clinic was established at Diakonhjemmet Hospital, Oslo, Norway, in 2003. The multidisciplinary team included rheumatologists, nurses, health secretaries, occupational therapists, physical therapists, pharmacists, orthopaedic surgeons and a dietician. Over a two year period, approximately 300 patients with OA were referred to the OA clinic by their general practitioners or specialists. Of these 300, 73 patients were followed for 1 year [15]. Most (78%) of these patients were women (mean age 61 years (range 24-92)). More than 60% reported to have pain in their knees and/or hands, while 40% had pain primarily localized to the hip. Approximately one fourth of the patients used NSAIDS and/or other types of analgesics. At the one year follow-up, 95% of the patients were very satisfied with the team care received, and pain and functioning was moderately improved [15]. This first evaluation with an open longitudinal design without a control group warranted the need for a more systematically and thorough evaluation of the effect and cost-benefits of this multidisciplinary, coordinated outpatient OA clinic.

The number of referrals to the clinic increased in the pilot period. To meet patients' need for information, a brief group-based educational programme was developed. Thus, in the updated multidisciplinary OA clinic, starting from 2005, patients first receive a 3.5 hours group education. After a lunch brake, they have individual consultations with a rheumatologist and thereafter, dependent on identified needs, also have encounters with other health professionals.

Few other studies have evaluated the effect of group-based educational programmes for OA in combination with a pragmatic individual approach, especially in a setting of a randomised clinical trial (RCT) [13].

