## Methods

Patients are randomised into the two interventions within three strata: patients with primary hand, hip or knee problems. A project coordinator includes patients and coordinates the patient-reported data collection with questionnaires. Health professionals who are taking part in the two interventions are not involved in the data collection. Blinding of providers and patients is not possible in this type of study, but the outcome assessors as well as those who perform the follow up telephone call are blinded. All patients involved in the project have signed an informed consent and have been informed according to the Helsinki declaration. The data inspectorate and the regional ethical committee (REK) reviewed and approved the project (REK ref 156-06073 1.2006.598); the ISRCTN trial number is 25778426.

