### Data analysis

#### Power calculations

As no satisfactory data on patient satisfaction and cost-effectiveness were available, power calculations were based on the secondary outcome pain with data from the pilot study and previous research on OA from our group [26-28]. In this RCT we compare two independent equally sized groups. We assume comparable variation in both groups, set alpha to 5%, beta to 80%, and assume a smallest clinical important difference between the groups of 0.20 based on an estimated difference for pain measured by WOMAC/AUSCAN. The standardized difference (0.20)/SD (0.70)) will be 0.25. According to the Altman nomogram, approximately 200 patients will be needed in each of the two treatment groups.

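### The choice between a parametric and a rank analysis of 4-month satisfaction is left to the observed data with no criterion; one model should be fixed now, with ANCOVA for outcomes that have a baseline

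*Protocol article*

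**What the plan says.** Under Statistical analyses the protocol states: "Both parametric and nonparametric statistical analyses will be used, dependent on how the variance is distributed". The sentence covers all outcomes alike. The same paragraph says that the effect analyses are run without knowing which intervention each group received, that intention-to-treat applies, and that "exploratory analyses will be performed to study the treatment effect within the three subgroups hip, knee and hand OA".

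Four other places bear on the point:

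- **Methods:** "Patients are randomised into the two interventions within three strata: patients with primary hand, hip or knee problems".
- **Primary outcomes and Table 2:** satisfaction is an 11-point scale from 0 to 10, collected at 4 and 12 months but not at inclusion.
- **Hypotheses, item 4:** pain, global disease activity, SF-36, WOMAC and AUSCAN are described in terms of changes, and no difference between the clinics is predicted. Table 2 shows pain, WOMAC/AUSCAN, PSFS and SF-36 collected at inclusion and at both follow-ups.
- **Background:** in the pilot, "95% of the patients were very satisfied with the team care received" at one year.

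**The concern.** A parametric comparison estimates a difference in means; a rank test addresses a shift in ranks. On a bounded, skewed scale the two can differ in size and in significance. A rule that picks between them from the trial's own outcomes, without saying what is inspected or what triggers which test, leaves the quantity being estimated open until the data are in. The stated trigger does not help, because the usual reason for choosing ranks is the shape of the distribution, not how a variance is distributed.

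The open choice is also unnecessary. If nearly all pilot patients were very satisfied, scores piled up near 10 are to be expected in at least the multidisciplinary arm.

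The second issue is precision. If the secondary outcomes are analysed as raw changes, as Hypothesis 4 suggests, the intervals are wider than those obtainable from the same data by adjusting the follow-up score for its baseline. That matters more for a hypothesis of no difference, which is informative only if the interval is narrow.

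**Working it through.** **1. The protocol's own sample size (pain).** Inputs from Power calculations: difference 0.20, SD 0.70, alpha 5% (two-sided assumed), power 80% (printed as beta), equal groups.

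- 0.20/0.70 = 0.286, which needs 193 per arm. At 200 per arm, power is Φ(0.286 × √(200/2) − 1.96) = Φ(2.857 − 1.96) = 81.5%.
- The protocol prints "The standardized difference (0.20)/SD (0.70)) will be 0.25". A value of 0.25 would need 252 per arm and gives 70.5% power at 200. That mismatch is a separate matter. I use 0.286 because it follows from the stated difference and SD and agrees with approximately 200 per group.

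**2. What an open choice of test does to type I error.** 10,000 simulated null trials of 200 per arm, t-test and Mann-Whitney, nominal 5%. The pretest is Shapiro-Wilk in each arm. The shapes are assumed. The Monte Carlo standard error is √(0.05 × 0.95/10,000) = 0.002.

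| Outcome shape | t-test | Mann-Whitney | Chosen by pretest | Smaller p-value reported |
|---|---|---|---|---|
| Skewed 0-10 scale | 0.050 | 0.050 | 0.050 | 0.070 |
| Normal | 0.051 | 0.050 | 0.052 | 0.061 |
| Lognormal | 0.047 | 0.050 | 0.050 | 0.079 |

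A choice made by rule costs essentially nothing in error rate. A free choice between two p-values raises it to 6.1% to 7.9%.

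**3. Change score against ANCOVA.** Let r be the correlation between baseline and follow-up, with equal SDs at both times. The protocol gives no r; 0.4 to 0.7 is assumed. In units of the follow-up variance, the change score has variance 2(1 − r) and ANCOVA has 1 − r². Their ratio is 2(1 − r)/(1 − r²) = 2/(1 + r). Power at 200 per arm is Φ(2.857/√variance − 1.96), reading the SD of 0.70 as that of a follow-up score.

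| r | Change variance | ANCOVA variance | Ratio | Power, change | Power, ANCOVA |
|---|---|---|---|---|---|
| 0.4 | 1.20 | 0.84 | 1.43 | 74% | 88% |
| 0.5 | 1.00 | 0.75 | 1.33 | 81.5% | 91% |
| 0.7 | 0.60 | 0.51 | 1.18 | 96% | 98% |

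These figures are for pain, a secondary outcome. They do not carry over to satisfaction, which has no baseline score.

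**4. Joint subgroups.** If the three strata were equal (assumed; about 67 per arm), power within one joint at 0.286 SD is Φ(0.286 × √(67/2) − 1.96) = 38%. With the same true effect in every joint, the chance that one or two of the three reach significance is 1 − 0.38³ − 0.62³ = 71%. Comparing within-joint p-values would therefore often suggest a difference between joints where none exists.

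**The case against.** - **The analyst is blinded to arm labels, and a pretest keeps type I error at 5%.** Both are true, and they keep this point modest. But a two-sided p-value is the same whichever label a group carries, so blinding does not stop a choice between two results. The text states no pretest or other discipline. It does not propose picking the smaller p-value either; it only fails to exclude it.
- **A reader might infer that the planned analysis is unstratified.** The document does not support this. The statistical section names no model, and a condensed article may leave covariates to a fuller plan that is not shown. Even if the strata were ignored, the test would be slightly conservative: true size 2Φ(−1.96/√(1 − R²)), or 4.4% to 3.9% if joint explained an assumed 5% to 10% of the variance.
- **A reader might infer that baseline scores go unused.** They do not: they enter through the changes in Hypothesis 4 and through changes in EQ-5D utility in the co-primary outcome. Hypothesis 4 is also the wording of a hypothesis and does not rule out ANCOVA.
- **The pilot figure is indirect.** It comes from patients followed for one year in a single uncontrolled clinic, and the pilot's response scale is not given. It makes a ceiling likely, not certain, and says nothing about the control arm.
- **The subgroup analyses are labelled exploratory.** This stands. The remaining risk lies in how their results are read.

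**Conclusion.** The point holds in a limited form. The protocol positively states a data-dependent choice of test family with no criterion, and this leaves the comparison of 4-month satisfaction unfixed. The cost in error rate is nil under a disciplined rule and about 1 to 3 percentage points if the more favourable result is reported, under the simulated shapes. The larger issue is that the meaning of the effect estimate is decided late when it could be decided now.

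For outcomes with a baseline, ANCOVA is never less precise than a change score in large samples. The gain in power for pain runs from about 14 points at r = 0.4 to about 2 points at r = 0.7, given a true difference of 0.286 SD, equal SDs at both times, no dropout and an assumed r. The protocol offers no basis for quantifying any gain for satisfaction.

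This is an improvement available at no cost, not an error that invalidates the trial.

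**What to change.** Replace the sentence on parametric and nonparametric analysis with a fixed specification:

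1. **Satisfaction at 4 months:** a linear model with arm and the joint stratum used in randomisation, reporting the mean difference with a robust or bootstrap confidence interval. At about 200 per arm this tolerates the expected skew. A stratified rank test is the sensitivity analysis. No baseline term, since none is collected.
2. **Pain, WOMAC/AUSCAN, SF-36 and PSFS:** ANCOVA of the follow-up score on arm, its own baseline and, where more than one stratum contributes, joint stratum. Reword Hypothesis 4 to match; it does not name PSFS, but Table 2 shows that PSFS has a baseline.
3. **Joints:** base any claim that effects differ by joint on an arm-by-joint interaction test, and show the within-joint estimates descriptively with intervals.

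Also state that the test-choice rule does not apply to cost-effectiveness, which needs mean costs and mean utility changes.

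The cost is analysis wording only. The strata and baseline scores are already collected, and the Time schedule places the analysis after data collection, so the wording can be settled before outcomes are examined.

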## Discussion

To our knowledge, this will be one of the first RCT's that will examine how a multidisciplinary approach affects treatment outcomes for patients with OA. Primary outcome will be patient satisfaction with health service assessed at 4 months, while, cost-effectiveness will be the co-primary outcome assessed at 12 months, and various aspects of health status are the secondary outcomes at both time-points.

A rheumatologist and a project coordinator examine all referrals to the multidisciplinary OA clinic at Diakonhjemmet Hospital. Patients aged 18-80 years are recruited to the study by a screening-form for OA based on clinical criteria of OA in hand hip or knee. Patients who may be eligible for the study receive oral and written information about the methods and aims of the study and are informed that participation is voluntary and can be terminated at any time without stating a reason and without any impact on their care. Informed consent will be obtained from all patients. They receive questionnaires by mail before the clinical examinations and if they have problems answering questions, a project assistant at the first encounter provide assistance. A smaller self-reported questionnaire on function, pain and health status will be mailed to the patients for the 4- and 12-month assessments.

All health professionals in the multidisciplinary team are represented among the staff at the Department of Rheumatology and a research secretary will be responsible for performance of practical aspects and organisation.

### Time schedule

Data collection is ongoing, and will be completed within 2011 which will be followed by a one-year period of data analyses and manuscript preparation.

The project will, by means of a randomised controlled trial, contribute to new knowledge on the effect of patient education for patients with OA. The project will also contribute with cost-effectiveness analyses comparing the two different methods of outpatient care.
